#### Primary outcome variables

Mindfulness: The Five Facet Mindfulness Questionnaire (FFMQ), with 39 items (range: 39–195 points) and five subscales: observing, describing, acting with awareness, non-judging of inner experience, and non-reactivity to inner experience. Higher total values indicate better full mindfulness [31–33].Self-compassion: The Self-Compassion Scale (SCS). The abbreviated scale of the Spanish version will be used, validated by García-Campayo et al. [34, 35], with 12 items scored with a Likert scale (1 to 5), which measures how the subject usually acts towards himself in difficult times. It consists of six subscales: self-friendliness, common humanity, mindfulness, and their opposites: self-judgement, isolation, and over-identification. Higher total values indicate more self-compassion.Work stress: An ordinal scale ranging from 0 (no stress level) to 10 (maximum stress level) and the Perceived Stress Questionnaire (PSQ) will be used. This questionnaire, validated by Sanz-Carrillo et al. [36], evaluates six factors: Tension-Instability-Fatigue; Social Acceptance of Conflicts; Energy and Fun; Overload; Self-fulfilment Satisfaction; Fear and Anxiety. The instrument consists of 30 items that participants answer according to the frequency with which each occurs in their lives, from 1 “almost never” to 4 “almost always”. The questionnaire is evaluated for two different periods (one recently and one in the last two years or in the last year). It classifies the subject at low, medium, or high risk.Burnout: the Maslach Burnout Inventory-General Survey (MBI-GS) questionnaire, with 22 items (range: 0–140 points) and three subscales: emotional exhaustion (EE), with nine items and a maximum score of 54 points; depersonalisation (DP), with five items and a maximum score of 30 points; and personal fulfilment (PF), with eight items and a maximum score of 48 points [37]. This instrument, translated into Spanish, it has been validated by Gil Monte [38].Empathy: the Jefferson Scale of Physician Empathy (JSPE) [39, 40]. This instrument is a multidimensional scale including 3 areas: taking perspective, compassionate attention, and “ability to put oneself in the patient’s shoes”. This scale consists of 20 items, which are determined using a Likert scale of 7 points.

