## Objective

The objective of the MINDUUDD study is to evaluate the effect of a mindfulness and self-compassion training programme on the levels of work stress and burnout in residents and tutors of Family and Community Medicine and Nursing. This study is based on the hypothesis that an abbreviated 4-session programme of mindfulness and self-compassion is at least as effective as the standard 8-session programme to increase mindfulness and reduce the levels of work stress and burnout of AP residents and tutors.

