### Sample size

To calculate the sample size, we have drawn on a previous study [25], using as an outcome variable the mean FFMQ score [31]; accepting an alpha risk of 0.05 and a beta risk of 0.2, in a bilateral contrast, 38 subjects are required in each group to detect a difference ≥ 15 points in the FFMQ scale between both experimental groups (EG4 and EG8) and the CG. It is assumed that the common standard deviation is 20. A loss or withdrawal rate of 25% has been estimated [43]. Because this is a cluster randomisation study, we have considered the design effect. The design effect multiplies the sample size by a factor ranging from 1.5 to 3 to achieve the same power, depending on the relationship between intra- and intergroup variance [44]. Estimates of the intra-cluster correlation coefficient (ICC) in randomised clinical trials in AP are generally < 0.05 [45]. This ICC, for a cluster size of 15, results in a design effect corresponding to a factor of 1.7. Assuming this value, the final study sample size would be at least 130 subjects. One hundred and thirty-two (132) professionals will be included, 44 in each comparison group, 22 for each teaching unit.

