### Statistical methods

The descriptive statistics of baseline characteristics of study participants and of questionnaire results—both before and after the intervention—will include means, standard deviations and ranges, medians and interquartile ranges, or frequencies and percentages, according to the variables. The fit of quantitative variables to the normal distribution will be checked by the Kolmogorov-Smirnov test. Prior to testing the effectiveness of the intervention, appropriate statistical tests will be used to examine possible baseline differences between groups (age, sex, time worked, profession, year of residency, previous mindfulness training). A per-protocol analysis will be performed in which all subjects who have completed at least 6 of the 8 sessions in EG8, or 3 of the 4 sessions in EG4, will be considered. All signalment analyses will be intention-to-treat in order to control for non-random dropout effects. Patterns of missing values ​​will be inspected and, if applicable, replaced using appropriate statistical methods.

To compare pre- and post-intervention results, a bivariate analysis will be performed, using Student’s t-test or the Wilcoxon test to compare related samples. Pre-post differences in the results of the questionnaires between the groups will be compared using ANOVA for repeated measures. Finally, a multivariate analysis will verify the effect of the interventions, adjusting for presumably predictive and/or confounding variables. To accomplish this, a multilevel linear regression will be used. The level of statistical significance will be set at *p* < 0.05 for all statistics. The analyses will be performed with SPSS version 17.0 and MLwiN version 3.00 software.

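### Five unranked primary constructs (eight or nine scores) are all tested at an unadjusted 0.05, while the trial is sized on the FFMQ alone

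*Protocol article*

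**What the plan says.** Under the heading "Primary outcome variables" the protocol article lists mindfulness (FFMQ), self-compassion (SCS), work stress, burnout (MBI) and empathy (JSPE). It gives no order and no lead score. Two constructs carry more than one score:

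- **Work stress:** "An ordinal scale ranging from 0 (no stress level) to 10 (maximum stress level) and the Perceived Stress Questionnaire (PSQ) will be used". On the PSQ it adds: "The questionnaire is evaluated for two different periods (one recently and one in the last two years or in the last year".
- **Burnout:** the MBI is described "with 22 items (range: 0–140 points) and three subscales". The subscale maxima are 54, 30 and 48.

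Statistical methods states: "The level of statistical significance will be set at" p < 0.05, and applies this to all statistics. Groups are compared by repeated-measures ANOVA and then by multilevel regression. There are three arms.

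The Sample size section proceeds by "using as an outcome variable the mean FFMQ score", comparing each experimental group with the control group (CG). The Objective is "to evaluate the effect of a mindfulness and self-compassion training programme on the levels of work stress and burnout". The hypothesis sentence that follows adds an increase in mindfulness and says that the short programme is no less effective than the long one.

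**The concern.** With several co-equal primary outcomes, a plan needs a rule for success: any one of them, all of them, or a fixed order. The article gives none, and it sets a single unadjusted threshold for everything. The two simple readings both cause trouble. If any one significant result suffices, the false-positive risk for the trial as a whole is well above 5%. If all must be significant, that risk is contained, but the 80% power planned for one score no longer describes the trial.

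The gap also affects the main claim. The design section calls the trial non-inferiority, and the article does not say which of the five constructs decides whether four sessions match eight. Work stress and burnout, named in the Objective, have no size or power calculation.

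**Working it through.** **Inputs.** From Sample size: difference 15 FFMQ points, SD 20, two-sided alpha 0.05, power 80%, loss 25%, 38 per group. From Primary outcome variables: the list of scores. From Statistical methods: 0.05 for all tests. From Study design: three arms. Correlation between scores is not given, so it is an assumption, varied from 0 to 0.7.

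**1. The plan's own figure.** n = 2 × [SD × (z₀.₉₇₅ + z₀.₈₀) / difference]² = 2 × [20 × (1.960 + 0.842) / 15]² = 27.9, so 28 evaluable per group. Allowing for loss, 28 / 0.75 = 37.3, so 38. The stated 38 is reproduced. It spends the full 0.05 on one comparison of one score.

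**2. Number of scores.** FFMQ 1 + SCS 1 + 0-10 stress scale 1 + PSQ 2 + MBI 3 + JSPE 1 = 9. With one PSQ period it is 8.

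**3. Any-one-wins, independent scores, one test each.** 1 − 0.95⁵ = 22.6%; 1 − 0.95⁸ = 33.7%; 1 − 0.95⁹ = 37.0%.

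**4. Any-one-wins, allowing for correlation and shared arms.** Simulation under no effect: 100,000 runs, three equal arms, normal scores with equal pairwise correlation ρ, each test at 0.05, no clustering. Chance of at least one significant result:

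| Scores | Tests per score | ρ = 0 | ρ = 0.3 | ρ = 0.5 | ρ = 0.7 |
|---|---|---|---|---|---|
| 5 | one omnibus three-arm test | 22.7% | 21.1% | 18.4% | 15.2% |
| 5 | EG4 and EG8 each vs CG | 37.9% | 35.0% | 31.0% | 25.4% |
| 5 | all three pairwise | 47.9% | 44.4% | 39.4% | 32.4% |
| 9 | one omnibus three-arm test | 37.0% | 33.0% | 27.5% | 20.8% |
| 9 | EG4 and EG8 each vs CG | 57.4% | 51.9% | 43.9% | 34.0% |
| 9 | all three pairwise | 69.0% | 62.9% | 53.6% | 42.1% |

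The lowest entry is about three times 5%.

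**5. All-must-succeed.** Alpha is not inflated. As an illustration, if each of five outcomes had 80% power and they were independent, joint power would be 0.8⁵ = 33%. It would reach 80% only if they were perfectly correlated. The article gives no power for the other four.

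**6. Keeping all primaries with a Bonferroni correction.** Using the formula in step 1 with the FFMQ inputs, before any design effect:

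- Five constructs, alpha 0.05/5 = 0.01: 42 evaluable, 42/0.75 = 56 with loss. Power at 28 evaluable is 59%.
- Nine scores, alpha 0.05/9 = 0.0056: 47 evaluable, 47/0.75 = 63 with loss. Power at 28 evaluable is 51%.

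**7. MBI range.** 54 + 30 + 48 = 132, against a stated upper limit of 140.

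**The case against.** **This belongs in the analysis plan.** A condensed article may leave multiplicity to the SAP. Here, though, the article itself calls five constructs primary and fixes one threshold for all tests. An SAP that ranked the outcomes or adjusted alpha would have to depart from this text.

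**The inflation is conditional.** This stands. It arises only if one significant primary is enough, and the article does not say so. The percentages also concern tests of difference, so they do not measure the error of the EG4-versus-EG8 non-inferiority claim.

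**Three pairwise contrasts are not specified.** This stands too. The ANOVA is closer to one omnibus test per score, and the sizing names only the two comparisons with CG. The omnibus rows are therefore the ones nearest the text.

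A reader might also draw four stronger conclusions that the article does not support:

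- *Error of 54% or 75%*, from 1 − 0.95¹⁵ and 1 − 0.95²⁷. These treat three contrasts that share arms as independent. Even with uncorrelated scores the simulation reaches only about 48% and 69%.
- *The FFMQ is foreign to the trial's aim.* It is absent from the Objective's first sentence, but mindfulness is part of the hypothesis.
- *A summed MBI will be analysed and its opposing subscales will cancel.* A total range is given, but no such analysis is stated.
- *Both PSQ periods are separate endpoints and the long one cannot show an effect.* The article describes how the questionnaire is scored and refers to an additional file, not shown here. A long recall window would dilute a recent change, not exclude it.

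**Conclusion.** The point holds in a limited form. Five constructs are primary without hierarchy, every test is at an unadjusted 0.05, and only the FFMQ was sized. On the any-one-wins reading, the chance of at least one false positive is roughly 15-37% under the analysis closest to the text, and 32-69% if all pairwise contrasts are made. Each range runs from five constructs at ρ = 0.7 to nine scores at ρ = 0, with clustering ignored. On the all-must-succeed reading the cost falls on power instead.

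It would be wrong to infer that a positive result is likely to be a chance finding, because the article does not say how success will be declared. The defect is that the text leaves this open while fixing the threshold. The MBI range is a real internal inconsistency, but a minor one that does not bear on multiplicity.

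**What to change.** 1. Name the FFMQ total at the post-intervention visit as the single primary outcome. It was sized and it is part of the hypothesis, so the per-group calculation of 28 evaluable (38 with loss) keeps its alpha of 0.05.
2. State the order of contrasts: for example, each experimental group against CG, as sized, with the EG4-versus-EG8 non-inferiority comparison given its own stated place in that order.
3. Then test two key secondaries in fixed order: work stress by the recent-period PSQ score, and one prespecified MBI subscale. The sponsor should choose the subscale, since the article gives no basis for preferring one.
4. Report SCS, JSPE, the 0-10 scale and the remaining MBI subscales as secondary, without confirmatory claims.
5. Report the MBI by subscale and correct its stated range to agree with the maxima, which sum to 132.

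**Cost.** The changes are to wording and testing order, and no questionnaire need be dropped. The downside is that fewer outcomes can support a confirmatory claim, and claims on stress and burnout depend on the FFMQ succeeding first. If the sponsor would rather lead with stress or burnout, the trial should be sized for that outcome.

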#### Secondary outcome variables

Anxiety or depression disorders: the Goldberg Anxiety and Depression Scale (GADS), validated for the Spanish population [41]. This instrument has 2 subscales, each with nine questions: an anxiety subscale (questions 1–9) and a depression subscale (questions 10–18). The first 4 questions of each subscale, questions 1–4 and questions 10–13, respectively, determine whether participants should try to answer the other questions.Self-perceived health status will be determined by a closed question, based on the one used in the Spanish National Health Survey [42]. Likewise, the participant’s feelings of loneliness, social and work isolation, and happiness, before and after the interventions, will be assessed by two closed questions with an ordinal qualitative scale.

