### Eligibility criteria

-Inclusion criteria: AP professionals who are active and give their informed consent to participate in the study.

-Exclusion criteria: Having previously attended a mindfulness training course or workshop of at least 4 weeks, being an active mindfulness practitioner, being on prolonged sick leave during fieldwork, or having mental disorders discouraging the intervention.

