### Outcomes and measures

The professionals will be asked to complete pre- and post-intervention questionnaires. The pre-intervention questionnaire will be filled out upon recruitment (baseline). The post-intervention questionnaire will be completed at 4 (EG4) or 8 weeks (EG8 and CG) after baseline and at 3 months after completion.

To measure the dependent variables or outcomes, the following instruments will be used (an additional file shows this in more detail [see Additional file 1]):

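### The skip rule in the anxiety and depression scale (GADS) suits screening better than the planned pre-post comparison of scores; asking all 18 items would avoid a truncated, jumping secondary outcome at little cost

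*Protocol article*

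**What the plan says.** Under Secondary outcome variables, the protocol article introduces the outcome as "Anxiety or depression disorders: the Goldberg Anxiety and Depression Scale (GADS), validated for the Spanish population". On its structure it says: "This instrument has 2 subscales, each with nine questions". It then sets the skip rule: questions 1–4 of the anxiety subscale and 10–13 of the depression subscale "determine whether participants should try to answer the other questions".

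The article gives no threshold for the skip rule, no score for unasked items and no case cut-off. Under Outcomes and measures it refers to a supplementary file for the instruments ("an additional file shows this in more detail"), which is not at hand.

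The Statistical methods section treats the questionnaires together. Within arms, results before and after are compared "using Student’s t-test or the Wilcoxon test to compare related samples". Between arms: "Pre-post differences in the results of the questionnaires between the groups will be compared using ANOVA for repeated measures". An adjusted multilevel linear regression follows, and the Abstract also names linear regression. None of these sentences excepts GADS.

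The trial recruits active primary care professionals and does not select them for anxiety or depression. It excludes those "having mental disorders discouraging the intervention".

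**The concern.** A two-step questionnaire is an economical way to screen: those with few positive answers early on need not go further. A change score needs something else, namely the same items answered by the same people at every visit. Under the skip rule, the number of items that contribute to a subscale depends on the participant's own early answers, and can differ between visits in one person.

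Two things follow if the sum is used as a quantitative outcome. Participants below the threshold have a compressed range, because symptoms on the last five items are never recorded. Participants who cross the threshold between visits show a change partly made by five items entering or leaving the score. The first can shrink the mean difference, and the second inflates the SD of change. At stake is the sensitivity of the secondary anxiety and depression comparisons.

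This is a data-collection rule. An analysis plan can say how to score unasked items, but it cannot recover answers that were never collected.

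**Working it through.** **Plan's own figure.** There is none for GADS. The Sample size section powers the mindfulness score (FFMQ) only.

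**Step 1: conditional items (from the document).** 9 − 4 = 5 per subscale, so 2 × 5 = 10 of the 18 questions depend on earlier answers.

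**Step 2: range and jump (arithmetic).** Let g be the number of positive answers out of four needed to continue, and count unasked items as 0.
- Below the threshold the score can only be 0 to g − 1.
- At or above it the score runs from g to 9.
- One extra positive answer at the threshold moves the score from g − 1 to between g and g + 5. The largest step is (g + 5) − (g − 1) = 6 points. It needs all five later items to be positive, so it is the extreme case.

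**Step 3: size (all inputs assumed).** The documents supply no threshold, prevalence, SD or effect. One subscale of nine yes/no items was simulated from a latent trait: 400,000 per arm, loading 0.6 to 0.75, pre-post trait correlation 0.7, true shift 0.5 SD, threshold 1 or 2. The required-n ratio is (d with all items / d with skip rule)², where d is the between-arm difference in change divided by its SD.

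Worked example, prevalence 0.3, loading 0.6, threshold 2 (65% skip):

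| Score | Difference | SD | d |
|---|---|---|---|
| All items | −0.86 | 2.25 | 0.382 |
| Skip rule | −0.78 | 2.59 | 0.302 |

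Ratio = (0.382 / 0.302)² = 1.60 (d taken before the other columns were rounded).

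Over prevalence 20-40%, the ratio is 1.14 to 1.34 with a threshold of 1 and 1.37 to 1.81 with a threshold of 2. Raising prevalence to 50% lowers the smallest ratio to 1.11. Over 20-50%, the share skipping is about 16-78%.

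**Step 4: a second set of assumptions.** 44 per arm, trait correlation 0.6, shift 0.6 SD, no clustering, t-test on change. Power with all items versus the skip rule:

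| Threshold | High symptoms | Low symptoms |
|---|---|---|
| 1 | 0.67 vs 0.66 | 0.36 vs 0.29 |
| 2 | 0.69 vs 0.61 | 0.37 vs 0.24 |
| 3 | 0.67 vs 0.54 | 0.36 vs 0.20 |

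At the two intermediate symptom levels with a threshold of 2, power is 0.66 vs 0.54 and 0.53 vs 0.39. Over all settings the loss is about 1 to 20 percentage points, and the share skipping at baseline runs from 7% to 94%.

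The mechanism depends on symptom level. With a threshold of 2 and low symptoms, the difference shrinks (−0.68 to −0.53) while the SD hardly moves (1.96 to 1.97). With high symptoms the raw difference does not shrink (−1.45 to −1.61), but the SD grows more (2.86 to 3.43).

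**The case against.** **The outcome may be case status.** The text speaks of disorders, gives GADS no score range (it does for FFMQ and the burnout scale), and the ANOVA sentence does not name GADS. If GADS is analysed as case or non-case, the change-score argument may not apply. This stands as a condition on the point. It does not remove it, because the only between-arm methods stated for questionnaires are quantitative.

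**Scoring detail may lie in the supplementary file or an analysis plan.** That is true, and its absence from a condensed article is not criticised here. The skip rule itself is stated in the article and limits what can be collected.

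**The skip rule is presented as part of a validated instrument.** Using it is therefore no error or contradiction. But a format that suits screening need not suit measuring change.

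**Stronger readings that a reader might infer.**
- That many participants will skip the later items. The documents give no prevalence or threshold. The eligibility criteria make a sizeable share plausible, but the Abstract and Background describe high work stress and burnout, which points the other way.
- That a definite loss of power follows. Its size rests wholly on assumed inputs, and no power is claimed for GADS.
- That low-level symptoms cannot be registered. Four items per subscale are asked of everyone.
- That one arm is favoured. The rule is the same in all arms, and no between-arm bias is shown.

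**Conclusion.** The point holds as a minor, conditional one. The skip rule and the quantitative questionnaire analysis are both in the article and fit poorly together. If the sum is analysed as change with unasked items counted as 0, truncation and a jump at the threshold follow by arithmetic. The consequence is extra noise and a smaller standardised effect in the secondary anxiety and depression comparisons. The primary outcomes and the sample size are unaffected.

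The size is not fixed by the documents. Under assumed item prevalence of 20-50% and a threshold of 1 or 2, about 1.1 to 1.8 times as many participants would be needed for the same power. When symptoms are common and the threshold is 1, the loss can be negligible (power 0.66 against 0.67).

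**What to change.** In the data collection notebook, have every participant answer all 18 GADS items, without a skip instruction, at each visit where GADS is given. Use the 0-9 subscale scores in the comparisons of the Statistical methods section. Derive the two-step screening classification afterwards from the same answers and report it as a proportion. The reverse is impossible: full scores cannot be rebuilt from answers that were skipped. The change therefore has to be made before data collection.

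The cost is one sentence in the protocol and at most ten extra yes/no questions per visit for those who would have skipped. The downside is a departure from the two-step administration format.

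If the two-step format is kept, the plan should state that GADS is analysed as case status or by an ordinal method and is excepted from the ANOVA. That deals with the jump in the change score but does not recover the unasked items.
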